
#### Study 1: Visit Procedures

After inclusion into the study, the patients will be pseudo-randomly placed into a vibrotactile sham or real vibrotactile condition by staff personnel, not affiliated with the study. Patients will take the MDS-UPDRS parts IB, II, PDQ-39, PDSS, and the UPSIT online and at home on medication 1–2 weeks before every study visit. Patients will be asked to complete a usability and tolerability questionnaire about the vCR device after receiving therapy for 1 week following the start of the trial. Patients will then retake this questionnaire 1–2 weeks before all subsequent study visits.

Study visits will occur at baseline, 3, 6 months, and after a 1-month pause in stimulation at 7 months. Patients will arrive off medication and perform the following assessments in order. The participant's health history, physiological and neurological state will be examined upon arrival. Then, patients will perform the MDS-UPDRS III and will be video recorded. Electroencephalography recordings, the VTDT and speech assessments will be administered. Patients will then perform objective measurements including Kinesia ONE and the APDM. Parcopa is then given, and patients receive a 1-h break. The following assessments will be done on medication following the 1-h break. The MDS-UPDRS parts IA, III, IV, Kinesia ONE, and the APDM.

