### Study 1 Design: Main Phase—Double Blind Sham-Controlled

We will perform a 7-month, double-blind, sham-controlled study including 30 PD patients randomly placed into either active vCR (*n* = 15) or a sham (*n* = 15) condition. All personnel and PD patients will be completely blinded to which stimulation pattern patients obtain. Parkinson's patients will receive vCR or sham stimulation for a total of 4 h a day (2 times 2 h a day with a break in between the 2-h sessions) at home for 6 months. To measure long-term effects, patients will pause stimulation for 1 month after the 6-month follow-up appointment.

#### Assessments: Study 1

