The following outcome measures and their descriptions will be administered to patients. The *MDS-UPDRS parts IA, IB, II, III*, and *IV* (29). The MDS-UPDRS parts IA and IB concerns non-motor experiences of daily living, in which IA is assessed by the study's main MDS-UPDRS movement disorders evaluator and IB is self-reported. Part II is motor experiences of daily living and is self-reported. Part III is the in-person motor evaluation assessed by the study's main MDS-UPDRS movement disorders evaluator. In addition, part III will be video recorded and sent to the three blinded video MDS-UPDRS III raters. Patient recordings will be evaluated after each patient completes his or her 7-month visit. Video raters will additionally be blinded to the date of administration. Part IV incorporates patient details on motor complications with the study's main MDS-UPDRS movement disorders evaluators observations and judgements. The *PD Quality of Life Questionnaire-39* (*PDQ-39*) (32) is a self-report questionnaire that examines health related difficulties specific to PD in eight quality of life categories within the last month. The *Parkinson's disease sleep scale* (*PDSS-2*) (33) examines PD related sleep issues during the past week. The *University of Pennsylvania Smell Identification Test* (*UPSIT*) (34) is a smell test comprised of 40 odors, in which patients try to correctly identify the odorant presented. Patients will also take a tolerability and usability questionnaire regarding the vCR device. We will perform a *vibratory temporal discrimination task* (*VTDT*) that consists of two vibratory bursts, with one burst delivered to the index finger and one burst to the middle finger. Each burst will start randomly on either the index or middle finger. This procedure will be performed on the right and left hand separately. The patient is instructed to judge if he/she felt a delay between the two vibratory bursts. This task was designed as a possible calibration method for future vCR studies by serving as a sensitivity measure for vibratory temporal changes, in which reduced perceived vibratory time differences correspond to increased vibratory temporal discrimination. Patients will also undergo clinically established *speech and voice assessments*. Speech samples will be collected at a sampling rate of 44,100 Hz on a laptop using the Praat Speech Analysis program (Version 5.4, University of Amsterdam). To collect samples, a head-worn, unidirectional microphone will be placed over the participant's ears and the microphone will be adjusted so that it is 6 cm from the participant's mouth. Specific samples will include sustained vowel phonations, sentence and paragraph length reading passages, and spontaneous speech. From these samples, speech and voice assessments will be conducted including measures of articulatory precision, speech intelligibility, speech rate, auditory-perceptual ratings of voice, and acoustic measures of vocal fundamental frequency, vocal intensity, and fundamental frequency and intensity variability. Additionally, the sentence intelligibility portion of the Assessment of Intelligibility in Dysarthric Speech (AIDS) (35) and patient self-assessment scales of Communicative Participation Item Bank (CPIB) (36) and the voice handicap index (VHI) (37) will be collected. For objective measures, patients will perform the *Kinesia ONE* motor evaluation, which uses a wearable accelerometer to assess motor activities similar to the MDS-UPDRS III and record their Parkinson's medication intake. The *Ambulatory Parkinson's Disease Monitoring* (*APDM*)'s Mobility Lab system will be used to measure objective gait disturbances. Lastly, the patient will also complete three different types of tasks during which *EEG* will be recorded. The first is a *sensorimotor EEG task*, in which patients receive a single vibratory stimulus to a random finger (excluding the thumb) on their non-dominant hand and are instructed with their dominant hand to push the response pad as fast as possible when they feel the vibratory burst. Each finger receives an equal number of vibratory pulses (50 per finger, equaling 200 trials) in a randomized order. Cortically, we expect to look at motor evoked potentials in response to cued vibration and their amplitude and latency changes throughout the course of treatment. Reaction time will also be documented. Additionally, we will record *vibration-only evoked potentials* in which we look at how two different types of vibratory pulses (high- and low- amplitude) affect different motor and sensory areas of the brain. The last task will be a recording done while the patient is at rest (*spontaneous EEG*). Patients will receive either active vCR or sham depending on the condition to which they were randomly assigned. For this task, we want to replicate our previous finding of decreased high beta band power (21–30 Hz) (17) for patients who received real vCR and quantify differences in activated brain areas in response to sham or active vCR. The MDS-UPDRS III off medication will be used as our primary outcome measure. All other measures are considered secondary.

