**Figure 3 F3:**
[figure not shown]
Depicts study 1 procedures for the double-blind, sham-controlled vCR study. Patients will receive a General Health Survey which includes our inclusion/exclusion questionnaire and our dopamine dysregulation syndrome questionnaire developed for the purpose of our study *via* email 8–1 weeks prior to the screening visit. During the screening visit (8–4 weeks prior to baseline) patients will be consented and will arrive at Stanford off medication, to complete their physical/neurological examination and report their PD medical history. Patients will perform the MDS-UPDRS III off medication with the study's main movement disorders evaluator and then receive Parcopa (dopamine medication). Patients will then repeat the MDS-UPDRS III after 1 hour of taking medication. Patients will complete a vibratory intensity discrimination task to confirm that they do not have severe vibratory sensory abnormalities. The study's treating movement disorders neurologist will track patients for 4 weeks prior to their first clinical study visit (baseline) to confirm that their medication is stable. One to two weeks prior to every clinical study visit, patients will receive the following questionnaires/tests: MDS-UPDRS IB, II, UPSIT, PDSS, FOG, PDQ-39, and the usability/tolerability questionnaire of the vCR device. During the clinical study visits (baseline, 3, 6, and 7 months), patients will arrive to Stanford off medication and undergo the physical/ neurological examination, PD medical history, MDS-UPDRS III, EEG, VTDT, APDM, Kinesia ONE, and speech assessments. Patients are administered Parcopa and after 1 h perform the MDS-UPDRS III, IA, IV, Kinesia ONE, and APDM. After the 6-month visit, patients undergo a 1-month pause in stimulation to measure long term effects of vCR at the 7-month follow-up. During the entire length of the trial, patients will report their daily LEDD amount and starting from baseline will perform the Kinesia ONE motor evaluation at home one to three times a week for motor monitoring. *The Usability/Tolerability questionnaire is performed 1 week after the start of therapy and then 1-2 weeks before every study visit. **vCR glove administration occurs at baseline only.

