#### Study 1: Statistical Analysis and Anticipated Results

A sample size of 30 was selected as a starting number of patients for the clinical trial. A priori analysis indicated that for a sample size of 30, we would need a large effect size (*f* = 0.42) in order to reach statistical significance (*p* ≤ 0.05). In our previous study of six patients receiving vCR treatment for 3 months, using a paired samples *t*-test to compare MDS-UPDRS III scores pre- and post-treatment, the effect size was large (*d* = 1.011) (17). Based on this, our large *f* effect size of 0.42 may be reasonable. Nevertheless, an interim analysis will be performed by an un-blinded, experienced statistical research personnel, who is unaffiliated with the study team and does not report to any study team member, the principal investigator, nor any neurologist involved in the studies. This interim analysis will be performed when 16 patients have completed the 3-month mark, with eight belonging to the sham group and eight belonging to the vCR group. Results from the interim mixed factorial analysis of variance (ANOVA), will allow us to recalculate our desired sample size.

A 2 (sham vs. real vCR) by 4 (baseline, 3, 6, and 7 months) mixed factorial ANOVA will be done separately on the following measures: MDS-UPDRS I, II, III, IV, Levodopa equivalent daily dose (LEDD), EEG sensorimotor related evoked components, vCR resting EEG beta power response, vibratory temporal discrimination, speech assessments, UPSIT, PDSS, PDQ-39, FOG, and gait measurements obtained from the APDM Mobility Lab.

Statistically, for patients who received real vCR, we hope to see significant improvement in all measures by 6 months and expect to see no significant worsening when comparing assessments done after the pre-planned 1-month pause in stimulation at 7 months. In addition, we expect to see no significant improvements in the sham group patients.

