#### Remote Study Procedures

If the patient chooses to remain in the study, the following procedures will take place remotely in the patient's home. After the 7-month follow-up in study 1, the patient will be reconsented sent home with the vibrotactile device equipped with active vCR. The patient will stimulate as needed and as instructed using the parameters described above. Patients will take the online the PDQ-39, MDS-UPDRS parts IB and II, PDSS, FOG, and the usability and tolerability questionnaire of the vCR device. Patients previously in the sham condition will be given the usability and tolerability questionnaire 1 week after they start active vCR. Patients will complete all online questionnaires 1–2 weeks before every remote study visit. The patient will also continue to use the Kinesia ONE device one to three times a week so staff can monitor motor ability and report LEDD. The treating movement disorders neurologist will call patients after 1 month of stimulation to ask questions regarding the patients' treatment. At-home follow-up motor evaluations will take place at 10, 13, and 14 months *via* video meeting with the study's main MDS-UPDRS movement disorders evaluator. The study's treating movement disorders neurologist will additionally accompany the video call to check in on the patient. Depending on the type of medication, patients will go off medication (12–48 h) for these evaluations and perform the Kinesia ONE motor evaluation and the remote administration of the MDS-UPDRS IA, III, and IV (38). The remote MDS-UPDRS III will be our primary outcome measure, while all other measures are considered secondary. After 6 months of establishing a dosing regime, the patient will undergo a 1-month pause in stimulation and take his or her final online questionnaires and remote motor evaluation. The patient will mail his or her vCR device back to Stanford and will be thanked for his or her participation. For a detailed schematic of Study 2 events see Figure 4.

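### The month-7 home questionnaires are completed about two to three weeks into the pause, not after the full month, and the PDQ-39 recall reaches back before the pause

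*Protocol article*

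**What the plan says.** All references are to the Protocol article.

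- **Pause.** Under Study 1 Design, "patients will pause stimulation for 1 month after the 6-month follow-up appointment". Study 1: Visit Procedures adds: "Study visits will occur at baseline, 3, 6 months, and after a 1-month pause in stimulation at 7 months".
- **Questionnaire timing, Study 1.** Visit Procedures has MDS-UPDRS IB and II, PDQ-39, PDSS and UPSIT done "online and at home on medication 1–2 weeks before every study visit". The Figure 3 legend repeats the rule and adds FOG: "One to two weeks prior to every clinical study visit, patients will receive the following questionnaires/tests". Neither place exempts month 7.
- **Recall windows.** Assessments: Study 1 says that the PDQ-39 "examines health related difficulties specific to PD in eight quality of life categories within the last month" and that the PDSS-2 "examines PD related sleep issues during the past week". It gives no recall window for MDS-UPDRS IB, II or FOG. The UPSIT is a test of odor identification and has no recall window.
- **Use of the data.** Study 1: Statistical Analysis enters these measures in the 2 by 4 mixed ANOVA with month 7 as the fourth level. For active patients the authors "expect to see no significant worsening when comparing assessments done after the pre-planned 1-month pause in stimulation at 7 months".
- **Study 2.** Remote Study Procedures states: "Patients will complete all online questionnaires 1–2 weeks before every remote study visit". The Figure 4 legend repeats this. Remote visits include month 14, which follows a second one-month pause. The same section also mentions the final online questionnaires together with the last remote motor evaluation, after the pause, but sets no day.

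**The concern.** Month 7 is the only Study 1 visit that tests whether an effect outlasts stimulation. A lead of one to two weeks does little harm at months 3 and 6, when stimulation is continuing. At month 7 the state being measured began only one month earlier, so the same lead removes a large part of it.

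Two consequences differ in reach. All the home-completed measures reflect a shorter pause than their label says. The PDQ-39, with its month-long recall, also mixes experience from the stimulation period into a score labelled as post-pause. If benefit does fade after stimulation stops, both make the month-6 to month-7 change look smaller than a full-month comparison would. That is the direction the authors expect, and the timing cannot be repaired once the data are collected.

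**Working it through.** **Inputs from the article:** pause from the month-6 visit to the month-7 visit; lead L = 7 to 14 days; PDQ-39 recall of one month; PDSS-2 recall of 7 days.

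**Assumptions:** a month M of 28 to 31 days; the pause starts on the day of the month-6 visit; PDQ-39 recall R is either the same length as the pause month or 28 days.

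**The plan's own figure.** Month 7 minus month 6 is one month. This holds for everything done at the visit (L = 0): days off stimulation = M, and PDQ-39 overlap = 0 when R = M.

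**Home questionnaires.**
- Days off stimulation at completion = M − L.
- PDQ-39 days before the pause = max(0, R − (M − L)). With R = M this equals L.

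| M | L | Days off (share of M) | Overlap, R = M | Overlap, R = 28 |
|---|---|---|---|---|
| 28 | 14 | 14 (50%) | 14 (50%) | 14 (50%) |
| 28 | 7 | 21 (75%) | 7 (25%) | 7 (25%) |
| 30 | 14 | 16 (53%) | 14 (47%) | 12 (43%) |
| 30 | 7 | 23 (77%) | 7 (23%) | 5 (18%) |
| 31 | 14 | 17 (55%) | 14 (45%) | 11 (39%) |
| 31 | 7 | 24 (77%) | 7 (23%) | 4 (14%) |

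Time off stimulation is 14–24 days, or 50–77% of the pause, and never the full month. PDQ-39 overlap is 4–14 days, or 14–50% of the recall, and never zero.

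**PDSS-2.** Its week starts on pause day M − L − 7, which is 14 − 7 = 7 at the earliest. The window lies wholly inside the pause but ends on day 14–24 instead of day 28–31.

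**After the change.** The longest medication withdrawal in the article is 48 h, so completion 2–3 days before the visit would precede it (illustrative lead). With M = R = 30, days off = 27–28 and PDQ-39 overlap = 2–3 days (2/30 = 7% to 3/30 = 10%).

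**The case against.** Several points on the other side are sound and limit the finding.

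- **A constant lead keeps the month-6 and month-7 forms one month apart, under the same home, on-medication conditions.** This is true and worth preserving. But a statement about persistence depends on time since stimulation stopped, and that is two to three weeks.
- **A reader might infer that every questionnaire is contaminated by the stimulation period.** The article does not support this. Recall overlap can be shown only for the PDQ-39. For the others, the most that follows is a shorter pause.
- **A reader might infer that the persistence result will be wrong, or turn the overlap into a fixed share of lost benefit that goes unseen.** That would need benefit to vanish at once and patients to weight all days equally. The article does not show that benefit fades at all. Its Introduction reports one patient with no considerable motor change after a one-month pause, which settles the question neither way.
- **A reader might think the main persistence evidence is affected.** It is not. MDS-UPDRS III (the primary outcome), IA and IV, EEG, VTDT, speech, Kinesia ONE and APDM are done at the visit, after the full pause.
- **Part I combines IB from home with IA from the visit.** That gap exists at every visit and is not a fault of the pause.
- **Month 14 is less clear than month 7.** The sentence on final questionnaires in Remote Study Procedures can be read as placing them after the pause. It gives no day and does not override the one- to two-week rule, so the two need reconciling.
- **Moving the forms into the clinic visit would change the setting at one time point.** This stands, and it favours completion at home late in the pause.

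**Conclusion.** The concern holds in limited form. By the article's own timing rules, the month-7 home questionnaires measure a pause of about 14–24 days, while the analysis section treats month 7 as following a one-month pause. The month-7 PDQ-39 also covers about 4–14 days of the stimulation period. Only month and recall length are assumed, and the shortfall and the overlap persist across the whole range examined.

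The bias is conditional: if benefit fades during the pause, these measures would understate the loss, towards the expected absence of significant worsening. If benefit is stable, little changes. Only secondary self-completed measures are involved. For month 14 the finding is an ambiguity in the text. Because Study 2 allows as few as three sessions a week, any overlap there is with the stimulation period and not necessarily with days on which the patient stimulated.

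**What to change.** - **Month 7.** Keep the one- to two-week lead at baseline and months 3 and 6. For month 7, have MDS-UPDRS IB and II, PDQ-39, PDSS-2, UPSIT and FOG completed at home, on medication, in the last days of the pause, just before medication withdrawal starts and before the allocation is disclosed at the visit.
- **Month 14.** Reconcile the one- to two-week rule in Remote Study Procedures and the Figure 4 legend with the sentence on final questionnaires, and apply the same end-of-pause timing.
- **If the timing is kept.** Report these measures as reflecting a two- to three-week pause, and state that the month-7 PDQ-39 recall partly covers the stimulation period.

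The cost is one line in the visit schedule, a narrower completion window, and a lead time at month 7 that differs slightly from month 6. Home, on-medication completion is preserved.

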#### Study 1: At Home Therapy Procedures

During the first study visit, patients will be taught how to use, wear and adjust the vibrotactile device. Patients will then be sent home and asked to stimulate for a total of 4 h a day with a break in between each 2-h session (minimum 1-h break) for 6 months. At the end of the 6 months, patients will be asked to stop stimulation for 1 month. During the 7-month study, patients are asked to continue their prescribed medication as needed. If the patient would like to decrease his or her medication due to positive motor results throughout the study, the patient can reduce medication according to the advice of our study's treating movement disorders neurologist and the patient's personal movement disorders neurologist. While at home, patients will have their own Kinesia ONE system to log medication information and perform motor tasks while on medication 1–3 times every week to monitor movement ability. After the start of the study, patients will have a 1-month checkup with the study's treating movement disorders neurologist over the phone to check in on how the participant is doing. If the participant experiences any worsening of motor ability/or side effects that he/she believes is due to the vibrotactile device after the 1-month checkup, the patient can schedule a phone call with the study's treating movement disorders neurologist to discuss what the next steps will be. In the event the participant experiences an adverse event or a serious adverse event either related or unrelated to glove, he/she is required to schedule a call with the study's treating movement disorders neurologist for evaluation within 3 days of the event. For a detailed schematic of study 1 events see Figure 3.

**Figure 3 F3:**
[figure not shown]
Depicts study 1 procedures for the double-blind, sham-controlled vCR study. Patients will receive a General Health Survey which includes our inclusion/exclusion questionnaire and our dopamine dysregulation syndrome questionnaire developed for the purpose of our study *via* email 8–1 weeks prior to the screening visit. During the screening visit (8–4 weeks prior to baseline) patients will be consented and will arrive at Stanford off medication, to complete their physical/neurological examination and report their PD medical history. Patients will perform the MDS-UPDRS III off medication with the study's main movement disorders evaluator and then receive Parcopa (dopamine medication). Patients will then repeat the MDS-UPDRS III after 1 hour of taking medication. Patients will complete a vibratory intensity discrimination task to confirm that they do not have severe vibratory sensory abnormalities. The study's treating movement disorders neurologist will track patients for 4 weeks prior to their first clinical study visit (baseline) to confirm that their medication is stable. One to two weeks prior to every clinical study visit, patients will receive the following questionnaires/tests: MDS-UPDRS IB, II, UPSIT, PDSS, FOG, PDQ-39, and the usability/tolerability questionnaire of the vCR device. During the clinical study visits (baseline, 3, 6, and 7 months), patients will arrive to Stanford off medication and undergo the physical/ neurological examination, PD medical history, MDS-UPDRS III, EEG, VTDT, APDM, Kinesia ONE, and speech assessments. Patients are administered Parcopa and after 1 h perform the MDS-UPDRS III, IA, IV, Kinesia ONE, and APDM. After the 6-month visit, patients undergo a 1-month pause in stimulation to measure long term effects of vCR at the 7-month follow-up. During the entire length of the trial, patients will report their daily LEDD amount and starting from baseline will perform the Kinesia ONE motor evaluation at home one to three times a week for motor monitoring. *The Usability/Tolerability questionnaire is performed 1 week after the start of therapy and then 1-2 weeks before every study visit. **vCR glove administration occurs at baseline only.

